## Abstract

**Objective:**

To report the statistical analysis plan (first version) for the Balanced Solutions *versus* Saline in Intensive Care Study (BaSICS).

**Methods:**

BaSICS is a multicenter factorial randomized controlled trial that will assess the effects of Plasma-Lyte 148 *versus* 0.9% saline as the fluid of choice in critically ill patients, as well as the effects of a slow (333mL/h) *versus* rapid (999mL/h) infusion speed during fluid challenges, on important patient outcomes. The fluid type will be blinded for investigators, patients and the analyses. No blinding will be possible for the infusion speed for the investigators, but all analyses will be kept blinded during the analysis procedure.

**Results:**

BaSICS will have 90-day mortality as its primary endpoint, which will be tested using mixed-effects Cox proportional hazard models, considering sites as a random variable (frailty models) adjusted for age, organ dysfunction and admission type. Important secondary endpoints include renal replacement therapy up to 90 days, acute renal failure, organ dysfunction at days 3 and 7, and mechanical ventilation-free days within 28 days.

**Conclusion:**

This manuscript provides details on the first version of the statistical analysis plan for the BaSICS trial and will guide the study’s analysis when follow-up is finished.

## INTRODUCTION

The Balanced Solutions *versus* Saline in Intensive Care Study (BaSICS) Trial is a multicenter, randomized, factorial, clinical trial that will assess the effects of Plasma-Lyte 148 *versus* 0.9% saline as the fluid of choice in critically ill patients, as well as the effects of a slow (333mL/h) *versus* rapid (999mL/h) infusion speed during fluid challenges, on important patient outcomes. The original protocol paper emphasizing the importance of the study, and the rationale and inclusion/exclusion criteria has been published previously, but details of the statistical approach and reporting of obtained data were not described.^(1)^

This report aims to provide details of the BaSICS statistical analysis plan (SAP), based on protocol version 3. There are several challenges in designing a statistical analysis plan for this study due to its factorial design, the potential exclusion of patients after enrollment expected with the use of posterior consent, and the interplay between survival and intervention use. Finally, it is expected that some important mediators are involved in the possible effects of both interventions, and this SAP represents an opportunity to define, a priori, how they will be analyzed and reported. The main study´s hypothesis, for both arms, is that a balanced solution and slow infusion speed can reduce 90-day mortality in critically ill patients. This statistical analysis plan for the BaSICS trial aims to prevent statistical analysis bias arising from exploratory analyses after the study results are known. It was prepared before the end of follow-up for all included patients by an independent statistical analyst without knowledge of the interim analysis conducted by the data monitoring committee.

### Study background and flowchart

BaSICS is a large pragmatic critical trial that aims to provide evidence for or against the use of Plasma-Lyte 148 over 0.9% saline and of lower infusion speeds during fluid challenges in critically ill patients. Patients were randomized using a web-based system designed for the trial in a factorial way (blocks of 12 patients), stratified by recruiting site in a 1:1:1:1 ratio to both define a specific fluid group (Plasma-Lyte 148 or 0.9% saline) and slow (333mL/h) or rapid (999mL/h) infusion during a fluid challenge.^(1)^ The details of the inclusion and exclusion criteria have been addressed in the original protocol, together with recommendations for fluid management and safety rules.^(1)^ The planned flowcharts for both interventions are shown in figures 1 and 2, respectively. BaSICS is a large pragmatic trial, and a screening log was not obtained at each site due to the large number of included patients and for local logistics reasons.

**Figure 1 f1:**
[figure not shown]
Plasma-Lyte *versus* saline.

**Figure 2 f2:**
[figure not shown]
Infusion speed.

Blinding to fluid type was possible due to identical bags manufactured by Baxter LA® labeled “A” to “F” (six types, with half of the letters saline and half Plasma-Lyte 148). Sites were instructed to use the study fluid for the fluid challenge, maintenance and, whenever possible, for the dilution of all drugs (if compatible) that required an infusion volume over 100mL. Use of fluid bolus and fluid management was left to the discretion of the attending physician due to the pragmatic nature of the trial; however, guidelines and good-clinical practices in fluid management were provided to the sites in the study material and were discussed during the investigator´s meetings. Infusion speed could not be blinded.

The answers to these two questions are important because it is presently unclear whether balanced (low chloride) solutions are beneficial for critically ill patients and because no large clinical trial has ever assessed the effects of varying infusion speeds on robust patient-centered outcomes.

### Sample size calculation, interim analyses and database lock

BaSICS was designed to enroll 11,000 patients. The sample size was calculated estimating 35% mortality within 90 days in the control group (saline and rapid infusion). This was based on data from large Brazilian cohorts, as discussed in the study protocol.^(1)^ The defined sample size allowed for an 89% power to detect a hazard ratio of 0.9 for both interventions assuming no interaction was expected among the study interventions.

Four interim analyses were performed in BaSICS. The first analysis of the first 1,000 patients aimed exclusively at checking the safety of the fluid speed comparison. Three other interim analyses followed at 25% (2,750 patients), 50% (5,500 patients) and 75% of the sample size (8,250 patients). We used very restrictive rules for stopping the trial for efficacy and we shall not adjust p-values for sequential tests (Appendix 1). A database lock will be applied after 90-day follow-up of all patients is obtained and all needed actions to obtain follow-up have been deployed. The baseline features of the included patients will be displayed as in table 1.

**Table 1 t1:** Baseline characteristics of the patients

Characteristics	Plasma Lyte		0.9% Sodium chloride	
	Slow infusion (n = xxx)	Rapid infusion (n = xxx)	Slow infusion (n = xxx)	Rapid infusion (n = xxx)
Age (years)	xx.x ± xx.x	xx.x ± xx.x	xx.x ± xx.x	xx.x ± xx.x
Female sex	xx.x (xx.x)	xx.x (xx.x)	xx.x (xx.x)	xx.x (xx.x)
Weight (kg)	xx.x ± xx.x	xx.x ± xx.x	xx.x ± xx.x	xx.x ± xx.x
Height (m)	xx.x ± xx.x	xx.x ± xx.x	xx.x ± xx.x	xx.x ± xx.x
Source of admission to ICU				
Elective surgery	xx.x (xx.x)	xx.x (xx.x)	xx.x (xx.x)	xx.x (xx.x)
Nonelective surgery	xx.x (xx.x)	xx.x (xx.x)	xx.x (xx.x)	xx.x (xx.x)
Emergency Department	xx.x (xx.x)	xx.x (xx.x)	xx.x (xx.x)	xx.x (xx.x)
Ward	xx.x (xx.x)	xx.x (xx.x)	xx.x (xx.x)	xx.x (xx.x)
Another hospital	xx.x (xx.x)	xx.x (xx.x)	xx.x (xx.x)	xx.x (xx.x)
Another ICU	xx.x (xx.x)	xx.x (xx.x)	xx.x (xx.x)	xx.x (xx.x)
APACHE II	xx.x [xx.x - xx.x]	xx.x (xx.x - xx.x]	xx.x (xx.x - xx.x]	xx.x [xx.x - xx.x]
SOFA	xx.x [xx.x - xx.x]	xx.x [xx.x - xx.x]	xx.x [xx.x - xx.x]	xx.x [xx.x - xx.x]
Mechanical ventilation				
Noninvasive mechanical ventilation > 12 hours	xx.x (xx.x)	xx.x (xx.x)	xx.x (xx.x)	xx.x (xx.x)
Invasive mechanical ventilation	xx.x (xx.x)	xx.x (xx.x)	xx.x (xx.x)	xx.x (xx.x)
Serum creatinine (mg/dL)	xx.x ± xx.x	xx.x ± xx.x	xx.x ± xx.x	xx.x ± xx.x
Cirrhosis or acute liver failure	xx.x (xx.x)	xx.x (xx.x)	xx.x (xx.x)	xx.x (xx.x)
Heart failure	xx.x (xx.x)	xx.x (xx.x)	xx.x (xx.x)	xx.x (xx.x)
Time from ICU admission to randomization (days)	xx.x [xx.x - xx.x]	xx.x [xx.x - xx.x]	xx.x [xx.x - xx.x]	xx.x [xx.x - xx.x]
Balanced crystalloid and saline administration in the 24 hours before enrollment				
Balanced solution				
Proportion of patients who received fluid	xx.x (xx.x)	xx.x (xx.x)	xx.x (xx.x)	xx.x (xx.x)
Fluid volume (mL)	xx.x [xx.x - xx.x]	xx.x [xx.x - xx.x]	xx.x [xx.x - xx.x]	xx.x [xx.x - xx.x]
Saline				
Proportion of patients who received fluid	xx.x (xx.x)	xx.x (xx.x)	xx.x (xx.x)	xx.x (xx.x)
Fluid volume (mL)	xx.x [xx.x - xx.x]	xx.x [xx.x - xx.x]	xx.x [xx.x - xx.x]	xx.x [xx.x - xx.x]
Predefined subgroups				
KDIGO criteria for acute kidney injury ≥ 1	xx.x (xx.x)	xx.x (xx.x)	xx.x (xx.x)	xx.x (xx.x)
Sepsis	xx.x (xx.x)	xx.x (xx.x)	xx.x (xx.x)	xx.x (xx.x)
Traumatic brain injury	xx.x (xx.x)	xx.x (xx.x)	xx.x (xx.x)	xx.x (xx.x)
Surgical patients	xx.x (xx.x)	xx.x (xx.x)	xx.x (xx.x)	xx.x (xx.x)
APACHE II ≥ 25	xx.x (xx.x)	xx.x (xx.x)	xx.x (xx.x)	xx.x (xx.x)
Receipt of > 1000mL of saline in the 24 hours prior to randomization	xx.x (xx.x)	xx.x (xx.x)	xx.x (xx.x)	xx.x (xx.x)

ICU - intensive care unit; APACHE - Acute Physiology and Chronic Health Evaluation; SOFA - Sequential Organ Failure Assessment; MAP - mean arterial pressure; KDIGO - Kidney Disease Improving Global Outcomes. Results expressed as mean ± standard deviation, n (%) or median [interquartile range].

### BaSICS inclusion and exclusion criteria

#### Inclusion criteria

To be randomized, patients must meet all of the following inclusion criteria: need for fluid resuscitation/plasma expansion and the clinician considers that Plasma-Lyte 148 or saline are equally appropriate for the patient, with no specific indications or contraindications for any of the fluids or for rapid or slow infusion; patients are not expected to be discharged on the day after their admission; at least one of the following risk factors for acute kidney injury (AKI):

- Age ≥ 65 years.- Hypotension (mean arterial pressure - MAP < 65mmHg or systolic blood pressure - SBP < 90mmHg) or the use of vasopressors.- Sepsis, defined as Sepsis 3 criteria.^(2)^- Use of invasive mechanical ventilation or of continuous noninvasive mechanical ventilation (including a high-flow nasal cannula) > 12 hours.- Oliguria (< 0.5mL/kg/hour for ≥ 3 hours).- Serum creatinine ≥ 1.2mg/dL for women or ≥ 1.4mg/dL for men.- Liver cirrhosis or acute liver failure.

#### Exclusion criteria

Were excluded: patients age < 18 years; acute renal failure treated with renal replacement therapy (RRT) or expected to require RRT within the next 6 hours; severe electrolyte disturbances (serum sodium ≤ 120mmol/L or ≥ 160mmol/L); death considered imminent and inevitable within 24 hours; with suspected or confirmed brain death; under exclusive palliative care and those previously enrolled in the BaSICS study

### Planned statistical analysis for the primary, secondary and tertiary endpoints

All clinical endpoints shall be presented as similar as possible to those shown in table 2. Categorical variables will be presented as the number and percentage. Continuous variables will be presented as the mean and standard deviation for variables such as age and physiological parameters (blood pressure, sodium and potassium levels). We will favor the presentation of ordinal variables, such as Sequential Organ Failure Assessment (SOFA) score, as the median and interquartile range. An alpha of 5% and 95% confidence intervals will be used unless otherwise stated; similarly, all analyses will be based on the intention-to-treat principle unless otherwise stated. Analyses will be performed with the latest R version available at the end of the patients’ follow-up (most probably version 4.0).

**Table 2 t2:** Outcomes comparing slow versus fast infusion speed and Plasma-Lyte versus 0.9% sodium chloride

Characteristics	Plasma-Lyte	0.9% Sodium chloride	Effect measure	p value*	Slow infusion	Rapid infusion	Effect measure	p value†	p value‡
			(95%CI)		(n = xxx)	(n = xxx)	(95%CI)		
Primary outcome									
90-day mortality	xx.x (xx.x)	xx.x (xx.x)	x.xx (x.xx - x.xx)	x.xx	xx.x (xx.x)	xx.x (xx.x)	x.xx (x.xx - x.xx)	x.xx	x.xx
Secondary outcomes									
Acute renal failure with need for renal replacement therapy within 90 days									
Incidence (per 1000 patient-day)	xx.x	xx.x	x.xx (x.xx - x.xx)	x.xx	xx.x	xx.x	x.xx (x.xx - x.xx)	x.xx	x.xx
At day 1	xx.x (xx.x)	xx.x (xx.x)		-	xx.x (xx.x)	xx.x (xx.x)		-	-
At day 2	xx.x (xx.x)	xx.x (xx.x)		-	xx.x (xx.x)	xx.x (xx.x)		-	-
At day 3	xx.x (xx.x)	xx.x (xx.x)		-	xx.x (xx.x)	xx.x (xx.x)		-	-
At day 7	xx.x (xx.x)	xx.x (xx.x)		-	xx.x (xx.x)	xx.x (xx.x)		-	-
In hospital (at least one renal substitution in hospital stay)	xx.x (xx.x)	xx.x (xx.x)	x.xx (x.xx - x.xx)	x.xx	xx.x (xx.x)	xx.x (xx.x)	x.xx (x.xx - x.xx)	x.xx	x.xx
Unknown at 90-day follow up	xx.x (xx.x)	xx.x (xx.x)		-	xx.x (xx.x)	xx.x (xx.x)		-	-
Lost contact for 90-day follow-up	xx.x (xx.x)	xx.x (xx.x)		-	xx.x (xx.x)	xx.x (xx.x)		-	-
Incident renal failure (using KDIGO ≥ 2) at day 3	xx.x (xx.x)	xx.x (xx.x)	x.xx (x.xx - x.xx)	x.xx	xx.x (xx.x)	xx.x (xx.x)	x.xx (x.xx - x.xx)	x.xx	x.xx
KDIGO ≥ 2 or death at day 3	xx.x (xx.x)	xx.x (xx.x)	x.xx (x.xx - x.xx)	x.xx	xx.x (xx.x)	xx.x (xx.x)	x.xx (x.xx - x.xx)	x.xx	x.xx
Incident renal failure (using KDIGO ≥ 2) at day 7	xx.x (xx.x)	xx.x (xx.x)	x.xx (x.xx - x.xx)	x.xx	xx.x (xx.x)	xx.x (xx.x)	x.xx (x.xx - x.xx)	x.xx	x.xx
KDIGO ≥ 2 or death at day 7	xx.x (xx.x)	xx.x (xx.x)	x.xx (x.xx - x.xx)	x.xx	xx.x (xx.x)	xx.x (xx.x)	x.xx (x.xx - x.xx)	x.xx	x.xx
SOFA > 2 at day 3									
Cardiovascular	xx.x (xx.x)	xx.x (xx.x)	x.xx (x.xx - x.xx)	x.xx	xx.x (xx.x)	xx.x (xx.x)	x.xx (x.xx - x.xx)	x.xx	x.xx
Neurologic	xx.x (xx.x)	xx.x (xx.x)	x.xx (x.xx - x.xx)	x.xx	xx.x (xx.x)	xx.x (xx.x)	x.xx (x.xx - x.xx)	x.xx	x.xx
Coagulation	xx.x (xx.x)	xx.x (xx.x)	x.xx (x.xx - x.xx)	x.xx	xx.x (xx.x)	xx.x (xx.x)	x.xx (x.xx - x.xx)	x.xx	x.xx
Respiratory	xx.x (xx.x)	xx.x (xx.x)	x.xx (x.xx - x.xx)	x.xx	xx.x (xx.x)	xx.x (xx.x)	x.xx (x.xx - x.xx)	x.xx	x.xx
Total SOFA score at day 3	xx [xx - xx]	xx [xx - xx]	x.xx (x.xx - x.xx)	x.xx	xx [xx - xx]	xx [xx - xx]	x.xx (x.xx - x.xx)	x.xx	x.xx
SOFA > 2 at day 7									
Cardiovascular	xx.x (xx.x)	xx.x (xx.x)	x.xx (x.xx - x.xx)	x.xx	xx.x (xx.x)	xx.x (xx.x)	x.xx (x.xx - x.xx)	x.xx	x.xx
Neurologic	xx.x (xx.x)	xx.x (xx.x)	x.xx (x.xx - x.xx)	x.xx	xx.x (xx.x)	xx.x (xx.x)	x.xx (x.xx - x.xx)	x.xx	x.xx
Coagulation	xx.x (xx.x)	xx.x (xx.x)	x.xx (x.xx - x.xx)	x.xx	xx.x (xx.x)	xx.x (xx.x)	x.xx (x.xx - x.xx)	x.xx	x.xx
Respiratory	xx.x (xx.x)	xx.x (xx.x)	x.xx (x.xx - x.xx)	x.xx	xx.x (xx.x)	xx.x (xx.x)	x.xx (x.xx - x.xx)	x.xx	x.xx
Total SOFA score at day 7	xx [xx - xx]	xx [xx - xx]	x.xx (x.xx - x.xx)	x.xx	xx [xx - xx]	xx [xx - xx]	x.xx (x.xx - x.xx)	x.xx	x.xx
Mechanical ventilation-free days within 28 days	xx [xx - xx]	xx [xx - xx]	x.xx (x.xx - x.xx)	x.xx	xx [xx - xx]	xx [xx - xx]	x.xx (x.xx - x.xx)	x.xx	x.xx
Tertiary outcomes	xx.x (xx.x)	xx.x (xx.x)	x.xx (x.xx - x.xx)	x.xx	xx.x (xx.x)	xx.x (xx.x)	x.xx (x.xx - x.xx)	x.xx	x.xx
Death in ICU									
Death in hospital	xx.x (xx.x)	xx.x (xx.x)	x.xx (x.xx - x.xx)	x.xx	xx.x (xx.x)	xx.x (xx.x)	x.xx (x.xx - x.xx)	x.xx	x.xx
Days in ICU (days)	xx.x (xx.x)	xx.x (xx.x)	x.xx (x.xx - x.xx)	x.xx	xx.x (xx.x)	xx.x (xx.x)	x.xx (x.xx - x.xx)	x.xx	x.xx
Days in hospital (days)	xx [xx - xx]	xx [xx - xx]	x.xx (x.xx - x.xx)	x.xx	xx [xx - xx]	xx [xx - xx]	x.xx (x.xx - x.xx)	x.xx	x.xx
Dias no hospital (dias)	xx [xx - xx]	xx [xx - xx]	x.xx (x.xx - x.xx)	x.xx	xx [xx - xx]	xx [xx - xx]	x.xx (x.xx - x.xx)	x.xx	x.xx

95%CI - 95% confidence interval; KDIGO - Kidney Disease Improving Global Outcomes; SOFA - Sequential Organ Failure Assessment; ICU - intensive care unit.

* p value for marginal comparison between Plasma-Lyte against 0.9% sodium chloride;

† p value for marginal comparison between slow infusion against rapid infusion;

‡ p value for interaction between saline and infusion speed. Results expressed as n (%) or median [interquartile range].

### Primary outcome analysis

Mortality until 90 days will be tested using mixed-effects Cox proportional hazard models, considering sites as the random variable (frailty models)^(3)^ adjusted for age, baseline SOFA^(4)^ score and the type of admission (planned admission, unplanned admission with baseline sepsis and unplanned admission without baseline sepsis). Sepsis will be defined as infection plus organ failure as per the Sepsis 3 criteria.^(2)^ Proportionality of the hazard ratio will be assessed using the Grambsch and Thernau method,^(5)^ and interactions between the intervention arms (infusion solution and speed) will be tested on this model. If the interaction parameter is significant, we intend to report only one manuscript describing “inside the table” effects, that is, exploring all the four possible combinations and their effects on mortality. If the interaction parameter is not significant at the 5% significance level, marginal effects for each group will be highlighted. In this case, “inside the table” effects shall be reported as supplementary material following CONSORT recommendations for 2 × 2 factorial designs.^(6,7)^ Kaplan-Meier curves will be presented comparing the four arms and separated considering only Plasma-Lyte® *versus* Saline, and Slow *versus* Rapid infusion. Patients with missing follow-up at 90-days will be added to the main primary outcome analysis and censored at their last known follow-up time, patients without discharge information will be imputed by chained equations method using site, age, baseline SOFA score and type of admission.

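### A 5% interaction pre-test decides which primary result leads, and the four-cell branch has no contrasts, multiplicity rule or success rule: type I error per question is 6.4% to 8.0% if one or either simple effect counts

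*SAP article*

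**What the plan says.** The Primary outcome analysis section fits a mixed-effects Cox model for 90-day mortality and tests the interaction between fluid type and infusion speed in it. Two branches follow.

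- Interaction not significant: "If the interaction parameter is not significant at the 5% significance level, marginal effects for each group will be highlighted". The four-cell effects then go to supplementary material, with a reference to CONSORT guidance for factorial trials.
- Interaction significant: a single manuscript on the within-table effects, "exploring all the four possible combinations and their effects on mortality". No reference cell, contrast, adjustment or criterion for a positive answer is given.

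The general rule in the section on planned analyses is "An alpha of 5% and 95% confidence intervals will be used unless otherwise stated", and nothing different is stated for the four-cell branch. The sample size section says "BaSICS was designed to enroll 11,000 patients" and claims "89% power to detect a hazard ratio of 0.9 for both interventions assuming no interaction was expected among the study interventions". It gives no power for the interaction test or for comparisons between cells.

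**The concern.** The result that leads the primary report depends on a test made on the same data. Under 1:1:1:1 allocation the marginal effect and the interaction are independent, but a simple effect (fluid at one speed, or speed with one fluid) is the marginal effect plus or minus the interaction. Once a trial has been selected for a large interaction, its simple effects are likely to look large too, even if nothing works.

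Two things are at stake. With no true effect, the two-stage procedure can exceed 5% per question. With a real and uniform benefit, a chance interaction can make it look confined to one stratum. The SAP's introduction gives as its purpose the prevention of bias from analyses chosen once results are known; a primary branch that is triggered by the data and left unspecified works against this.

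**Working it through.** **Inputs.** From the SAP: 11,000 patients, 35% control mortality at 90 days, hazard ratio 0.9 for each factor, 1:1:1:1 allocation, alpha 5%, interaction pre-test at 5%. Assumed: two-sided tests (sidedness is not stated; 95% intervals are), normal test statistics, no allowance for interim looks.

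**The SAP's own figure.** Mortality under hazard ratio 0.9 is 1 − 0.65^0.9 = 32.14%. Deaths: 5,500 × 0.35 + 5,500 × 0.3214 ≈ 3,693. Schoenfeld: √(3,693/4) × |ln 0.9| = 3.20; power = Φ(3.20 − 1.96) = 89.3%. If both factors work (3,540 deaths) it is 88.0%; with 35% mortality in all patients (3,850 deaths) it is 90.5%. The stated 89% reproduces.

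**Power of one simple effect.** Half the deaths, about 1,847: √(1,847/4) × |ln 0.9| = 2.26; Φ(2.26 − 1.96) = 61.9%, or 60% to 64% over the same event variants.

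**Type I error per question, no true effects.** Let a and b be the z-statistics of the two simple effects of one factor. They are independent; the marginal z is (a + b)/√2 and the interaction z is (a − b)/√2, which are also independent. Hence

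error = 0.95 × 0.05 + 0.05 × P(claim | interaction significant).

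The first term is 4.75%. Simulation (5 to 6 million draws) gives the conditional probability:

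| Rule in the four-cell branch | P(claim, given significant interaction) | Error per question |
|---|---|---|
| No claim made | 0 | 4.7% |
| One pre-named simple effect at 5% | 34% | 6.4% |
| Either of two, Bonferroni over four | 26% | 6.0% |
| Either of two, Bonferroni over two | 42% | 6.8% |
| Either of two at unadjusted 5% | 65% | 8.0% |
| *Marginal test always primary* | *not applicable* | *5.0%* |

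For the unadjusted rule: 0.0475 + 0.05 × 0.65 = 0.080.

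**True hazard ratio 0.9 in both strata, no interaction.** The interaction is still significant in about 5% of trials. Within those, at least one simple effect of the factor is significant in 99.6% and both in about 3%, so exactly one in about 96% (99.6 − 3.4). A pre-named one is significant in 52%.

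**Overall two-stage power at hazard ratio 0.9.** 89.8% if either simple effect counts, 87.4% if a pre-named one counts, 85.0% if both are needed.

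**The case against.** The strongest reply is that the four-cell branch is described as exploring, so no formal claim may be intended; the error rate is then 4.7% and nothing is inflated. That is a possible reading, but the SAP does not say so. The branch stands under the primary outcome and takes over its lead report, whereas the SAP labels its tertiary endpoints exploratory explicitly. If no claim is meant, neither question gets a confirmatory answer in that branch. The CONSORT reference does not settle it, because it is attached to the non-significant case.

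Four stronger readings are tempting and are not supported:

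- *That the marginal answers would be withheld.* The Table 2 shell gives marginal effects, intervals and p-values for both factors alongside the interaction p-value, and the Kaplan-Meier curves are planned for each margin as well as for the four arms. Neither depends on the interaction test. The marginal results are displaced from the lead, not suppressed.
- *That the error rate is 8%.* This is the top of the range. It needs either simple effect at unadjusted 5% to count, which the default alpha permits but no text states.
- *That the 89% is wrong.* It reproduces, and the SAP itself limits it to the case "assuming no interaction was expected among the study interventions".
- *That 8% error and 62% power occur together.* They belong to different rules. The rule that gives 8.0% loses no overall power (89.8%); the 62% is for a single pre-named simple effect, whose rule gives 6.4%.

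Whether average or cell effects should lead once an interaction is found is also partly a matter of judgement. That is a reason to settle it in advance.

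**Conclusion.** The point holds in limited form. A 5% interaction test decides which analysis is the headline primary result, and the four-cell branch is left without contrasts, multiplicity rule or success rule. Under the global null, error per question is 6.4% with one pre-named simple effect and 8.0% with either at the default alpha; Bonferroni rules fall at 6.0% to 6.8%. Of the rules examined, only making no claim in the branch stays under 5%. A uniform benefit would be shown as significant in only one stratum in about 96% of the roughly 5% of trials that enter the branch by chance.

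The consequence is moderate: the branch is rarely entered when there is no interaction, and overall power changes little. The figures rest on two-sided tests, balanced cells and large-sample normality.

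**What to change.** State in Primary outcome analysis that:

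1. the marginal hazard ratio of each factor, from the model with both main effects and no interaction term, is the primary result whatever the interaction p-value;
2. the interaction hazard ratio with 95% confidence interval and the four-cell table are always reported beside it;
3. cell-level effects are exploratory, with the contrasts named and multiplicity-adjusted p-values if they are tested.

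The exploratory label is needed as well as the adjustment: if cell-level results could still replace the marginal ones, Bonferroni over the four simple effects would leave about 6.0% per question. With the marginal tests always primary, error is 5.0% per question and the 89% power applies to the result that leads.

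The cost is a change of SAP wording; no new data or patients are needed. The downside is that under a true qualitative interaction the marginal hazard ratio is an average over opposing effects. The interaction estimate and the cell table make that visible.

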### Secondary outcomes

The following secondary endpoint analysis were defined:

- Renal replacement therapy up to 90 days.- Acute renal failure incidence defined as Kidney Disease Improving Global Outcomes (KDIGO)^(8)^ stage 2 or 3 evaluated at days 3 and 7. We plan to use both serum creatinine and diuresis for the KDIGO classification. Diuresis was collected on a daily basis during BaSICS, and therefore we will use the average diuresis over 24 hours as the urinary output criteria in KDIGO; creatinine criteria will be used if diuresis information is not registered. In case of a disagreement between creatinine and diuresis criteria for KDIGO, we will consider the worst criteria.- SOFA score assessed both as the total value and as individual components and each of their components separately (Cardiovascular, Neurologic, Coagulation, Hepatic and Respiratory) will be evaluated on day 3 and 7.- Mechanical ventilation-free days within 28 days.

Renal replacement therapy up to 90 days will be estimated using a mixed Poisson model adjusted for age, baseline SOFA and admission type and will be reported as the incidence per 1,000 patient-days. Alternatively, we will also report renal replacement therapy at 90 days in a competing risk model considering death as a competitor for the need for RRT. Incidence of AKI at days 3 and 7 will be tested with mixed generalized linear models with a binomial distribution and the logit link function (also known as a mixed logistic regression model^(9)^) considering site as a random effect; the results will be presented with odds ratios and 95% confidence intervals. Additional analysis combining KDIGO and death will be performed as a supportive analysis to address competitive risks issues.

SOFA score will be tested with a mixed generalized linear model using the distribution that best fits the data (Poisson, gamma, inverse gaussian, or multinomial, among others), and the results will be presented as the mean and/or median differences or ratios with respective 95% confidence intervals using the delta method. Organ dysfunctions at day 3 and 7 (specific SOFA item - cardiovascular, neurologic, coagulation and respiratory as a dichotomous variable defined as higher than 2) will be tested with mixed logistic regression models.

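### Primary outcome: the censoring and imputation rules overlap without precedence, and the imputation predictors omit the last day known alive and both randomised arms

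*SAP article*

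**What the plan says.** The primary analysis is time-to-event: "Mortality until 90 days will be tested using mixed-effects Cox proportional hazard models", with site as a frailty term and adjustment for age, baseline SOFA and admission type.

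One sentence at the end of the same section handles incomplete outcomes. Patients lacking 90-day follow-up stay in the analysis and are "censored at their last known follow-up time, patients without discharge information will be imputed by chained equations method using site, age, baseline SOFA score" and admission type. The sentence does not limit censoring to patients with a known discharge, does not say which rule comes first, and does not name the quantity to be imputed.

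Other sections bear on this but do not settle it:
- Secondary outcomes: the imputation of total SOFA uses the post-baseline SOFA trend, baseline characteristics and the study arms, with a sensitivity analysis that drops the arms. It does not extend to mortality.
- Secondary outcomes: post-baseline data exist. "Diuresis was collected on a daily basis during BaSICS", and SOFA is evaluated on days 3 and 7.
- Sensitivity analyses: the only one listed for the primary outcome is per protocol.
- Table 2: the rows for unknown or lost 90-day follow-up sit under renal replacement therapy and are descriptive.

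**The concern.** There are three related problems.

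1. **Overlap.** A patient with no discharge information and no 90-day contact satisfies the condition of each rule. Two analysts could treat that patient differently and both follow the plan.
2. **Predictors.** A patient seen alive for days or weeks has already survived part of the 90-day risk. A model with baseline predictors only ignores this. It also ignores the arms, so imputed outcomes carry no treatment effect and dilute the estimate.
3. **Entry into the model.** A Cox model needs a time and a status for each patient. The plan does not say what is imputed or how it becomes such a pair, and it has no safeguard against an imputed death dated before a day on which the patient was alive.

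At stake are a slightly attenuated hazard ratio and an unfixed rule for the primary endpoint. The article's Introduction says the plan exists to prevent analysis choices made after results are known.

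**Working it through.** **Step 1. Who falls under which rule, as written**

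| Discharge information | 90-day follow-up | Rule |
|---|---|---|
| present | present | none needed |
| present | missing | censor |
| missing | present | 90-day status known, so nothing should need imputing |
| missing | missing | censor and impute both apply |

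The last row is the overlap.

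**Step 2. Inputs from the SAP article**
- Sample size: "BaSICS was designed to enroll 11,000 patients".
- Control risk: "The sample size was calculated estimating 35% mortality within 90 days in the control group (saline and rapid infusion").
- Effect and power: "The defined sample size allowed for an 89% power to detect a hazard ratio of 0.9 for both interventions".
- Alpha: "An alpha of 5% and 95% confidence intervals will be used unless otherwise stated". Sidedness is not stated; two-sided is assumed.
- Allocation: "stratified by recruiting site in a 1:1:1:1 ratio", hence 1:1 for each marginal comparison (5,500 per side).

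**Step 3. The plan's own figure**
- Treated risk = 1 − 0.65^0.9 = 32.1%.
- Events = 5,500 × (0.350 + 0.3214) ≈ 3,693.
- Power = Φ(√3,693 / 2 × |ln 0.9| − 1.96) = Φ(3.20 − 1.96) = 89.3%.

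The stated 89% is reproduced and is not in question.

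**Step 4. Remaining risk of a patient known alive on day s**

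The article does not give the timing of deaths, so two shapes are assumed, each with 35% dead by day 90. Risk = 1 − exp{−λ(90^k − s^k)}, with λ = −ln(0.65)/90^k.

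| Alive to day | k = 0.5 (early deaths) | k = 1 (constant hazard) | Baseline-only imputation |
|---|---|---|---|
| 7 | 26.7% | 32.8% | about 35% |
| 14 | 23.0% | 30.5% | about 35% |
| 28 | 17.3% | 25.7% | about 35% |

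The overstatement per imputed patient is 35 − 32.8 = 2.2 to 35 − 26.7 = 8.3 points at day 7, and 35 − 25.7 = 9.3 to 35 − 17.3 = 17.7 points at day 28. It is close to zero for a patient last seen on the first day.

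**Step 5. Dilution from leaving out the arms**

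If a share f is imputed without reference to arm, the log hazard ratio shrinks by roughly (1 − f), giving HR = 0.9^(1−f). Power is then as in step 3.

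| f | HR | Power |
|---|---|---|
| 1% | 0.901 | 88.7% |
| 2% | 0.902 | 88.0% |
| 5% | 0.905 | 86.0% |
| 10% | 0.910 | 82.2% |

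**Step 6. Simulation of the two rules**

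Assumptions: 11,000 patients, two arms 1:1, k = 0.5, 35% control mortality, true HR 0.9, and a share f due to be lost at a uniform time between days 1 and 30 if still alive. There are no site effects or covariates, and 1,500 runs per setting. The imputation rule is read as drawing 90-day status without arm or days alive, with a death time borrowed from observed deaths.

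| f | HR, censoring | HR, imputation |
|---|---|---|
| 2% | 0.900 | 0.901 |
| 5% | 0.900 | 0.905 |
| 10% | 0.902 | 0.910 |

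The Monte Carlo standard error is about 0.0009 on the log scale. The imputed death risk was 33.6%, against a true risk of about 22% given survival to last contact. About 44 to 45% of imputed deaths fell before a day on which the patient was known to be alive.

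**The case against.** The sentence can be read as a hierarchy, the specific case overriding the general: discharge known but no 90-day contact means censor, discharge unknown means impute. That is sensible and gives each patient one rule. A reader who infers a flat contradiction therefore goes too far. But the hierarchy is not written down, and adopting it still leaves the predictor list as stated.

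A reader might also infer that the plan imputes a bare status with no event time. The text does not say so; it leaves the imputed quantity unnamed, and an analyst could impute a valid time. A condensed article may also leave such mechanics to a fuller document. That objection stands for the mechanics. It does not reach the overlap or the four-variable list, which the article states itself.

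Finally, censoring is not assumption-free. It requires non-informative loss, which is open to doubt when the missing item is the discharge outcome. This stands, and is a reason to keep a well-built imputation as a sensitivity analysis.

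**Conclusion.** The point holds as a rule for the primary endpoint that is not fully fixed and whose stated imputation predictors are poorly chosen. The bias is towards the null and small: a true hazard ratio of 0.900 becomes about 0.901, 0.905 or 0.910 with 2%, 5% or 10% of patients affected. Those shares, the timing of loss and the early-death pattern are assumptions. The article gives no count of patients without discharge information.

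Two stronger readings are not supported. The first is a spurious mortality difference between the open-label speed arms: that needs missing discharge information to differ by arm, and nothing in the article shows that it does. The second is a large overstatement of risk for every imputed patient: step 4 shows that this depends on how long each patient was observed alive and on the assumed timing of deaths.

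The change is still worth making before database lock. It is nearly free, and no planned sensitivity analysis tests the choice.

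**What to change.** Replace the sentence in Primary outcome analysis with one rule: in the primary Cox analysis, every patient without 90-day status, including those without discharge information, is censored at the last day documented alive.

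Keep imputation as a named sensitivity analysis that:
- draws event time and status jointly, conditional on survival beyond the last day documented alive;
- includes both study arms, as the SOFA imputation already does;
- adds the available day 2 to 7 data to site, age, baseline SOFA and admission type.

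Report the number of patients handled this way by arm, so that any imbalance can be seen.

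The cost is a sentence or two of SAP text and a simpler primary analysis. The downside is small: these patients contribute less follow-up, and the primary result relies on non-informative censoring, which the sensitivity analysis examines.
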